### Sample size

A sample size of 1,310 (655 in each group) is required for this trial. Internal Quitline service evaluations and previous findings from a cessation trial conducted by the Clinical Trials Research Unit have established that the average four week quit rate in people receiving usual care through Quitline is approximately 50% [31,32]. A non-inferiority margin of difference between the group proportions was set at 5% (i.e. the quit rates in the cytisine treatment group will be no worse than 5% less than the rate in the NRT active control group). A sample size of 1,310 will be sufficient to confer 90% power at the one-sided significance level of 0.025 using a binomial test for equivalence. The true four week quit rate in those who receive cytisine was assumed to be 55%, which is midway between the estimated efficacy of varenicline (60%) [8] and NRT [6]. The required sample size incorporates a 20% inflation factor to allow for a sufficiently large dataset to evaluate the intervention based on both the intention to treat as well as the per protocol population. The sample size is adequately powered to also evaluate the non-inferiority of cytisine on two month quit rates. Recruitment will take approximately 18 months based on previously run Quitline trials [32,33], and will aim for a minimum of 25% of participants to be Māori and 15% to be Pacific peoples. The sample size will allow the consistency of effects for Māori and Pacific peoples compared to non-Māori non-Pacific to be assessed.

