Following on from the recently published placebo-controlled trial by West et al. (2011) [17], an appropriate research question to now answer is how the efficacy of cytisine compares to NRT. Such a question is important from a policy and funding perspective to help decide whether to use cytisine as a first or second line agent for smoking cessation treatment or whether to publicly fund the drug. Based on the systematic review mentioned above, the expected difference in efficacy between cytisine (OR = 1.83, 95% CI 1.21 to 2.99)[14] and NRT (OR = 1.74, 95% CI 1.64 to 1.86) [6] is too narrow to feasibly conduct a head-to-head superiority trial. We therefore propose conducting a non-inferiority trial to demonstrate whether cytisine is at least as effective as NRT at increasing quit rates in dependent smokers motivated to quit.

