## Discussion

### Primary outcome assessment

The non-inferiority trial design precludes us from having a primary outcome based on six month quit rates. Loss to follow up and treatment non-compliance tends to reduce observed differences in treatment effect, which in non-inferiority trials biases findings away from the null. Later assessments are more likely to suffer from loss to follow up and treatment non-compliance, particularly as participants in the intervention group may use NRT after they have completed their 28 day course of cytisine if they feel it necessary to support their on-going quit attempt. Removing these participants from per protocol analysis of six month quit rates is likely to significantly reduce the power of the study. Instead the primary outcome will be based on a one month assessment of quit rates, with six month quitting variables collected as secondary outcomes.

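### The 90% power depends on cytisine being truly better than NRT by 4 to 5 points, which does not fit the odds ratios used to justify the non-inferiority design; on those odds ratios power is 53% to 62%

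*Protocol article*

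**What the plan says.** In the protocol article, the Sample size section states: "A sample size of 1,310 (655 in each group) is required for this trial". The control rate rests on service evaluations and an earlier trial: "the average four week quit rate in people receiving usual care through Quitline is approximately 50" per cent. The margin is 5 percentage points, the one-sided level 0.025 and the power 90%, with a 20% inflation so that both the intention-to-treat and the per-protocol populations can be evaluated. On the cytisine arm it says: "The true four week quit rate in those who receive cytisine was assumed to be 55" per cent, explained as halfway between varenicline (60%) and NRT.

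The Background takes a different expectation. It sets a pooled odds ratio against placebo of 1.83 (95% CI 1.21 to 2.99) for cytisine beside 1.74 (1.64 to 1.86) for NRT, and concludes that the expected difference "is too narrow to feasibly conduct a head-to-head superiority trial". That is the stated reason for a non-inferiority design.

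The Sample size section adds two further statements. On the later time point: "The sample size is adequately powered to also evaluate the non-inferiority of cytisine on two month quit rates". On Māori and Pacific participants against all others: "The sample size will allow the consistency of effects" to be assessed, with recruitment minimums of 25% and 15%.

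**The concern.** The article uses two expected effects. A small one, an odds ratio of about 1.05 between the drugs, selects the design. A larger one, an odds ratio of about 1.22, sizes it. The larger one comes from a midpoint with a different drug, and the text does not reconcile it with the Background.

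The choice matters because power in a non-inferiority trial depends on the sum of the true difference and the margin. Assuming +5 points with a 5-point margin doubles the distance being tested, from 5 to 10 points, and cuts the required sample size to about a quarter. A reader of the Sample size section would take the trial to have 90% power to show that cytisine is not materially worse than NRT. It has that power only if cytisine is in truth several points better. If the drugs are close to equivalent, as the Background expects, an inconclusive result is a likely outcome, and readers should know this beforehand.

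**Working it through.** **Inputs.** From Sample size: control 50%, cytisine 55%, margin 5 points, one-sided 0.025, power 90%, 20% inflation, 655 per arm. From Background: odds ratios against placebo of 1.83 and 1.74, and 1.93 for cytisine at 3 to 8 weeks. Assumption: the ratio of two odds ratios against placebo can be applied to the 50% control rate at four weeks. The non-inferiority limit is read as cytisine minus NRT = −5 points, as the Sample size section describes it.

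**1. The plan's own figure.**
n per arm = (1.96 + 1.2816)² × (0.50×0.50 + 0.55×0.45) / (0.05 + 0.05)² = 10.508 × 0.4975 / 0.01 = 522.7, so 523.
523 / 0.8 = 654 per arm, 1,308 in total, against 1,310 stated. This reproduces. (Multiplying by 1.2 instead gives 628 per arm, 1,256 in total, and does not.) Removing 20% from 655 leaves 524 per arm.

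**2. Cytisine rates implied by the Background.**
- 1.83 / 1.74 = 1.052; 1.052 / 2.052 = 51.3%
- 1.93 / 1.74 = 1.109; 1.109 / 2.109 = 52.6%
- For comparison, 55% against 50% is (0.55/0.45) / 1 = 1.22

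**3. Power.** Power = Φ[(d + 0.05)/SE − 1.96], with SE = √{(p_c(1−p_c) + p_t(1−p_t))/n}.
Example at 51.3%, n = 655: SE = √(0.4998/655) = 0.02762; 0.0626/0.02762 − 1.96 = 0.306; Φ = 62%.

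| True cytisine rate (NRT 50%) | 655 per arm | 524 per arm |
|---|---|---|
| 55% (Sample size) | 95% | 90% |
| 52.6% (3 to 8 week odds ratio) | 78% | 69% |
| 51.3% (odds ratios used to justify the design) | 62% | 53% |
| 50% (equal) | 44% | 37% |

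Simulating the confidence-interval rule (400,000 runs per case) at 55%, 51.3% and 50% agreed to within 1 percentage point. The true advantage needed for 90% power is 5.0 points at 524 per arm and 3.9 points at 655.

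**4. Interval width.** At 50% in both arms and 655 per arm: 1.96 × √(0.5/655) = 5.4 points. This exceeds the margin, so the observed difference must be at least about 5.4 − 5.0 = +0.4 points for the lower limit to clear −5.

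**5. Two months.** The article gives no two-month rate, so a control rate of 20% to 50% is assumed, with the same margin. If a 5-point advantage or the same odds ratio (1.22) persists, power is 90% to 97% at 524 per arm and 95% to 99% at 655. With no true difference it is 37% to 53% and 44% to 62%.

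**6. Ethnic groups.** The minimum shares give about 328 Māori, 197 Pacific and 786 other participants. Taking 50% and 55% in each group, the standard error of the difference in effect from the third group is √{0.4975 × (1/163.75 + 1/393)} = 0.0656 for Māori and √{0.4975 × (1/98.25 + 1/393)} = 0.0796 for Pacific participants. Multiplied by 2.80 (1.96 + 0.84), the interaction detectable with 80% power is 18 and 22 points.

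**The case against.** The strongest defence has four parts.

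First, the calculation is correct and the 55% is disclosed with a reason. This stands: the problem is an assumption at odds with the Background, and a reader who inferred a miscalculated sample size would be wrong.

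Second, the Treatment effects section makes intention-to-treat primary and counts those lost as smoking, so all 655 per arm contribute. This also stands. It would be wrong to say that the primary analysis needs a full 5-point advantage for 90% power; about 3.9 points is enough. That is still well above 1.3 or 2.6 points.

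Third, the 1.83 is a 3 to 6 month estimate, the comparison is indirect, and its interval is wide: 1.21/1.74 to 2.99/1.74 is 0.70 to 1.72, which contains 1.22. Two later placebo-controlled trials in the Background also report larger effects, though at 26 weeks and 12 months and with wide intervals. And a 5-point difference would itself need about 4,190 participants for 90% power in a superiority test, so calling the difference too narrow does not by itself exclude 5 points. These arguments show that 55% is possible. They do not make it the article's own expectation, and the short-term odds ratio still gives only 69% to 78%.

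Fourth, the two secondary statements are not refuted. On the 5-point assumption the two-month claim is met. A reader might cite the Discussion, where excluding participants who later use NRT "is likely to significantly reduce the power of the study", but that sentence concerns the six-month per-protocol analysis. The ethnic statement promises only that consistency can be assessed, and heterogeneity tests are planned; it states no power.

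**Conclusion.** The point holds as an internal inconsistency about the expected effect. The 90% power follows from the stated inputs but requires a true cytisine advantage of 3.9 points (655 per arm) to 5.0 points (524 per arm). On the odds ratios that justify the design, power is 62% or 53%; on the 3 to 8 week odds ratio, 78% or 69%; at equality, 44% or 37%. These figures assume a 50% control rate and that indirect odds ratios carry over to four weeks. The equality row needs only the first assumption.

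The two-month statement lacks a rate and a per-protocol loss and depends on the same advantage; it is unsupported, but the documents do not show it to be false. Subgroup precision is low, with detectable interactions roughly four times the margin, so a non-significant heterogeneity test would say little about consistency. No stated power claim is broken there.

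**What to change.** Keep 1,310 participants and change the text.

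- Reconcile the Background with Sample size: explain why about 1 point is expected when choosing the design and 5 points when sizing it, or adopt one expectation.
- State that 90% power is conditional on 55% against 50% (524 per arm; 95% at 655), and give power at 52.6%, 51.3% and 50% beside it, for both 655 and 524 per arm.
- State that, with rates near 50% and 655 per arm, the observed difference must be at least about +0.4 points to show non-inferiority.
- Make the two-month statement conditional on the same 5-point advantage, with a stated two-month rate and per-protocol loss, or remove it.
- Report differences with 95% confidence intervals for Māori, Pacific and other participants beside the heterogeneity test, and give the detectable interactions of about 18 and 22 points.

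The cost is a less favourable stated power. No participants, visits or data are added. For scale, 90% power at 51.3% would need 1,341 per arm before inflation (1,677 after division by 0.8), and at equality 2,102 (2,628).

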### Withdrawal criteria

Should participants require discontinuation of study treatment for any reason (see below), or if they elect to cease taking treatment, follow-up calls and data collection will continue as scheduled as if they were continuing with the randomised treatment. Participants may have the study treatment withdrawn if one or more of the following occurs:

• The participant makes a voluntary decision to withdraw from follow-up, or from the treatment.

• The participant has any serious clinical adverse event, concurrent illness, or other medical condition that indicates to the principal investigator that continued treatment with the study treatment is not in the best interest of the participant. The study treatment will be withdrawn if the participant develops any life threatening or seriously disabling illness or is admitted to hospital.

• The participant becomes pregnant during the course of the trial. Participants will be advised to stop taking their allocated treatment and discuss on-going use of smoking cessation products with their general practitioner or lead maternity caregiver.

• The principal investigator feels that it is in the best interests of the participant.

• The study is terminated.

If the participant discontinues treatment due to a serious adverse event, the participant will be followed until the event resolves or there is a return to a clinically acceptable medical status. Participant deaths or serious adverse events, which occur within 30 days of discontinuation, will be reported to the project co-ordinator.

### Data management

The design and management of all databases associated with this trial will be undertaken by the data management and information technology groups at the Clinical Trials Research Unit. The databases will be constructed in Oracle and internet database entry at Quitline (undertaken by the research assistants) will be via their in-house Filemaster system, from which the Unit receives hourly updates. Uploads will be stored in the Unit's Oracle database and linked to the electronic Case Record Form (CRF) data where applicable. Validation rules for each CRF will be specified by the project co-ordinator, in association with the senior data manager. These rules will include range checks so that inaccuracies in data collection can be identified early. A query will be raised as soon as any values are entered that are outside the allowed range or if data are missing. The research assistants at Quitline will amend the form as soon as a query is raised.

### Data monitoring

An independent Data Safety and Monitoring Committee (DSMC) will be established for this trial. Members of the committee will have no conflicts of interest and will not be directly involved with the trial. The DSMC will draw up their own terms of reference and will be free to review any information or study process in addition to the reviews of safety data. The study statistician will provide the committee with reports on safety data. An independent person will also monitor Quitline and the Clinical Trials Research Unit during the trial to ensure that the study protocol is adhered to. At Quitline the monitor will audit every randomised participant's records and ensure that study documentation is up-to-date and record keeping meets protocol and regulatory requirements. The monitor will visit Quitline early on during the study (after ten participants have been randomised), at study close-out and twice during the course of the trial. The monitor will audit the Clinical Trials Research Unit every three months to see that handling of the study medication is appropriate and correct documentation is kept.

### Data analysis

A senior biostatistician at the Clinical Trials Research Unit was involved in the sample size estimation, wrote the statistical analysis plan agreed upon by all members of the Steering Committee specifying *a priori *all analyses to be undertaken. Data from the trial will be entered into an Oracle database and all statistical analyses will be performed using SAS version 9.2 (SAS Institute Inc. Cary NC), and R. No interim analyses will be undertaken.

#### Baseline characteristics

Socio-economic status, smoking information, and mood and physical symptoms associated with withdrawal will be summarised and descriptive summary statistics provided. Since any differences between randomised groups at baseline could only have occurred by chance, no formal significance testing will be conducted.

#### Treatment effects

Non-inferiority will be evaluated by testing whether the lower bound of the 95% CI for difference in quit rates excludes a 5% difference. In particular, the proportion of participants that have been continuously abstinent at four weeks for both groups and the associated two-sided 95% CI for the difference will be estimated. Non-inferiority of cytisine over NRT will be accepted if the lower bound of the 95% CI around the estimated difference in the primary endpoint event rates lies above 5%. The primary analyses will be carried out on an intention-to-treat basis where participants lost to follow-up will be presumed to be smoking. However, it is increasingly recognised that non-inferiority studies should also be evaluated against a per protocol population defined on the basis of compliance, protocol violations, and missing data [34,35]. Both sets of results are important and will be considered when assessing the study objective. In the case that non-inferiority is evident, assessment as to whether cytisine is superior to NRT will be carried out using the same approach but comparing to a zero difference and applied to the intention to treat population.

Chi-squared analyses comparing the proportion of participants that have been continuously abstinent by treatment group, and incidence rates, RR, risk differences and 95% CI will be calculated. Subsequent secondary analyses involving adjustment for baseline covariates including stratification factors will be undertaken using logistic regression. The consistency of effects for Māori, Pacific peoples, and non-Māori non-Pacific will be assessed using tests for heterogeneity. The distribution of all continuous endpoints will be assessed for normality and skewed data will be subjected to an appropriate transformation before analysis. The change from baseline in symptoms of nicotine withdrawal, AUDIT-C and number of cigarettes smoked per day will be analysed using repeated measures models and adjustment for baseline value.

A pre-analysis review will be conducted before the primary analyses. The purpose of this review is to establish rules for a per protocol analysis and to reconsider the analysis plan (e.g., adjustment for potential confounders) in light of recent research. Any amendments (and the rationale) will be justified and documented in the statistical analysis plan. A per protocol analysis involves looking at the major protocol violations such as cross-over treatments, withdrawals and lost to follow-up. The per protocol population will consist of all randomized patients who have complied with the treatment allocated, were not lost to follow-up, and who do not have major protocol deviations pertaining to eligibility or the assessment of the treatment difference.

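### The written acceptance rule for non-inferiority sets the threshold at +5 instead of −5 percentage points and contradicts the protocol's own margin

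*Protocol article*

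**What the plan says.** The margin and its direction are in the Sample size section of the protocol article. The margin is 5%, explained as meaning that "the quit rates in the cytisine treatment group will be no worse than 5% less than the rate in the NRT active control group". With the difference taken as cytisine minus NRT, the lower confidence bound must therefore exceed −5 percentage points.

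The decision rule is in the Treatment effects section, which states it twice:

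- The opening sentence gives no sign: non-inferiority is evaluated by "testing whether the lower bound of the 95% CI for difference in quit rates excludes a 5% difference".
- The acceptance criterion then requires that the "lower bound of the 95% CI around the estimated difference in the primary endpoint event rates lies above 5"%. There is no minus sign, and the section does not say which rate is subtracted from which.

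The same section adds that, once non-inferiority is evident, superiority is assessed by the same method against a difference of zero.

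**The concern.** The two sections give different thresholds for the primary conclusion. Neither order of subtraction makes the written criterion agree with the margin:

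- **Cytisine minus NRT.** A lower bound above +5 shows that cytisine is better by more than 5 points. This is superiority by a margin, not non-inferiority.
- **NRT minus cytisine.** A lower bound above +5 shows that cytisine is worse by more than 5 points. A correct rule in this direction would use the upper bound and require it to be below +5.

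The written criterion also clashes with two other statements. The follow-on test against zero would be redundant, because a lower bound above +5 already excludes zero. And the Background section says the expected difference from NRT is too small for a superiority trial to be feasible, yet the literal rule asks for more than simple superiority.

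The main trial result is at stake. The stated power does not apply to the literal rule. The Cost analyses section also makes the cost work conditional on a positive primary outcome, so the threshold governs that as well.

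**Working it through.** **Inputs, all from the Sample size section**

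- NRT rate 50%: "average four week quit rate in people receiving usual care through Quitline is approximately 50"%.
- Cytisine rate 55%: "The true four week quit rate in those who receive cytisine was assumed to be 55"%.
- Margin 5 percentage points, with cytisine allowed to be lower.
- Power and level: "sufficient to confer 90% power at the one-sided significance level of 0.025 using a binomial test for equivalence".
- Size: "A sample size of 1,310 (655 in each group) is required for this trial".
- Inflation: "The required sample size incorporates a 20% inflation factor".

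**Step 1. Reproduce the stated sample size with the threshold at −5 points**

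The distance from the assumed true difference to the threshold is 0.05 − (−0.05) = 0.10. The normal quantiles are 1.960 and 1.282, and (1.960 + 1.282)² ≈ 10.507.

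- Pooled variance, mean rate 0.525: n = 2 × 0.525 × 0.475 × 10.507 / 0.10² = 524.06 per arm. Divided by 0.8 this is 655.07, or about 1,310 in total.
- Unpooled variance: n = (0.50 × 0.50 + 0.55 × 0.45) × 10.507 / 0.10² gives 523 per arm. Divided by 0.8 this is 654, or 1,308 in total.

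The figure of 1,310 is reproduced, with the 20% applied by dividing by 0.8. With the threshold at +5 the distance would be 0.05 − 0.05 = 0, and no finite sample size would give 90% power. The sample size was therefore calculated for −5.

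**Step 2. Probability of meeting each rule**

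Normal approximation: P = Φ((true difference − threshold)/SE − 1.96), with SE = √[(p_NRT(1 − p_NRT) + p_cyt(1 − p_cyt))/n].

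At 50% v 55% the numerator under the root is 0.25 + 0.2475 = 0.4975.

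- n = 655: SE = √(0.4975/655) = 0.02756
  - threshold −5: Φ(0.10/0.02756 − 1.96) = 95.2%
  - threshold +5: Φ(0/0.02756 − 1.96) = Φ(−1.96) = 2.5%
- n = 524: SE = √(0.4975/524) = 0.03081
  - threshold −5: Φ(0.10/0.03081 − 1.96) = 90.1%, the stated power
  - threshold +5: 2.5%

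The literal rule gives 2.5% at either size because the assumed true difference equals its threshold.

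**Step 3. Other true cytisine rates (NRT 50%, cytisine minus NRT)**

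| Cytisine rate | −5 rule, 524 / 655 per arm | +5 rule, 524 / 655 per arm |
|---|---|---|
| 45% | 2.5% / 2.5% | below 0.01% / below 0.01% |
| 50% | 36.6% / 44.0% | 0.02% / 0.01% |
| 55% | 90.1% / 95.2% | 2.5% / 2.5% |
| 60% | 99.8% / above 99.9% | 37% / 45% |

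The −5 rule has its nominal one-sided 2.5% error when cytisine is truly 5 points worse, as a non-inferiority test should.

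**Step 4. Observed difference needed at 655 per arm**

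- Threshold −5: −0.05 + 1.96 × 0.02756 = +0.004, or +0.4 points.
- Threshold +5: 0.05 + 1.96 × 0.02756 = +0.104, or +10.4 points.

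The two rules give opposite answers for observed differences between about +0.4 and +10.4 points. The planning value of +5 lies in the middle of that range.

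**The case against.** The strongest reply is that this is a slip of notation in a sound design. The Sample size section gives the margin in the right direction, the sample size reproduces only with that direction, and the stated aim is for cytisine to be at least as effective as NRT. The later test against zero makes sense only if the first threshold is below zero. A careful reader would supply the missing sign, and nobody would plausibly run the test as NRT minus cytisine. All of this stands. The 2.5% describes literal application of one sentence, not the design, and it depends on a true difference of exactly 5 points; at a true 10-point advantage the literal rule would be met 37% to 45% of the time.

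Two further replies carry less weight. First, the protocol refers to a separate statistical analysis plan, which may state the rule correctly. That is possible, but the protocol does not leave the rule to that plan: it states one, and the one it states is wrong. A correct plan would then disagree with the published protocol. Second, a minus sign may have been lost in text conversion. Comparison signs elsewhere in the article are intact, and the typeset page will settle the point.

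That the intended rule can be inferred does not remove the need to correct it. The protocol is where readers check that the threshold was fixed in advance, and it should not have to be deduced from another section.

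**Conclusion.** The criterion is wrong as written and must be corrected. It places the non-inferiority threshold at +5 points, whereas the margin, the sample size and the follow-on superiority step all require −5 points for cytisine minus NRT. Applied literally at the planning rates, it lowers the chance of declaring non-inferiority from 95.2% to 2.5% with 655 per arm, or from 90.1% to 2.5% with 524. It also raises the observed difference needed by 10 points. These figures assume true rates of 50% and 55%, a normal approximation with unpooled variance, and the difference taken as cytisine minus NRT. The contradiction between the two sections does not depend on any of those assumptions. The margin and sample size are not in question.

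**What to change.** In the Treatment effects section, replace the acceptance criterion with: *The difference is the cytisine quit rate minus the NRT quit rate. Non-inferiority is accepted if the lower bound of the two-sided 95% confidence interval lies above −5 percentage points; superiority is then claimed if, in the intention-to-treat population, it lies above 0.*

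Reword the section's opening sentence with the same sign and direction, and check that the statistical analysis plan carries the same rule. The cost is one or two sentences. Sample size, data collection and trial conduct do not change.

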### Blinding

Due to the nature of the intervention only single blinding (of researchers, not of participants) is possible. Members of the trial steering committee, management committee, and other study team members (with the exception of the project co-ordinator and the Quitline senior research manager) will remain blinded to treatment allocation until the code is broken (namely, after the last follow-up call is completed and the data recorded). The project co-ordinator will not be blinded as they will be responsible for distributing the cytisine to participants. The senior research manager and research assistants based at Quitline will not be blinded to treatment allocation, as they are required to know which group each participant has been allocated to in order to conduct the scheduled follow-up calls.

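### Non-inferiority rests on an ITT test that counts every lost participant as a smoker; the per-protocol result has no defined weight, and its rules may be settled after the code is broken

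*Protocol article*

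**What the plan says.** All references are to the protocol article.

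- **Treatment effects, decision rule.** Non-inferiority is accepted on the lower limit of the two-sided 95% interval for the difference in one-month continuous abstinence, judged against a 5-point margin. The primary analysis is ITT, and "participants lost to follow-up will be presumed to be smoking".
- **Treatment effects, per protocol.** A per-protocol evaluation is added: "Both sets of results are important and will be considered when assessing the study objective". Nothing is said about what is concluded if one set meets the margin and the other does not.
- **Treatment effects, pre-analysis review.** The per-protocol set is outlined: complied with allocation, not lost, no major deviation on eligibility or assessment. Its working rules come later: "The purpose of this review is to establish rules for a per protocol analysis and to reconsider the analysis plan". The review is timed only as preceding the primary analyses, and its amendments go into the statistical analysis plan.
- **Blinding.** Committee members and most of the study team stay blinded "until the code is broken (namely, after the last follow-up call is completed and the data recorded"). The project co-ordinator and the Quitline research staff are unblinded throughout.
- **Sample size.** "A sample size of 1,310 (655 in each group) is required for this trial", giving "90% power at the one-sided significance level of 0.025". The figure includes a 20% inflation so that both the ITT and the per-protocol populations can be evaluated.
- **Primary outcome assessment (Discussion).** "Loss to follow up and treatment non-compliance tends to reduce observed differences in treatment effect". This is the stated reason for not using six-month quit rates as the primary outcome.

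**The concern.** In a superiority trial, counting losses as failures is usually seen as cautious. In a non-inferiority trial it can work the other way. If the lost are not all smokers, equal loss scales both quit rates down and brings a true deficit closer to zero. Unequal loss adds a difference that has nothing to do with treatment. The article recognises that loss narrows differences, and it bought extra sample for a per-protocol evaluation. It then leaves open whether a failed per-protocol result would stop a claim that ITT supports.

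The per-protocol set is the counterweight to ITT here, and it protects the conclusion only if its exclusions are chosen without sight of allocation and outcome. The wording does not secure that. At stake is a claim that cytisine is no more than 5 points worse than NRT when it is in fact 5 points worse, made more often than the stated 2.5%.

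**Working it through.** **1. The plan's own figure.** Inputs from Sample size: 50% NRT, 55% cytisine, 5-point margin, one-sided 0.025, power 90%.

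n per arm = (1.960 + 1.282)² × (0.50×0.50 + 0.55×0.45) / (0.05 + 0.05)² = 523 after rounding up.

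Inflated: 523 / (1 − 0.20) = 654 per arm, or 1,308 in total, against 1,310 stated. This reproduces. Multiplying by 1.20 instead gives 1,256 and does not. A set reduced by 20% (655 × 0.80 = 524 per arm) has 90.1% power, so the trial is already sized for a per-protocol test.

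**2. Error of the ITT rule at the margin.** True one-month rates are set to 50% NRT and 45% cytisine, with 655 per arm. The article gives no expected loss, so the loss fractions L are assumptions. Let r be the chance of abstinence among the lost relative to those followed, with each arm's overall true rate p held fixed. With the lost counted as smokers, the rate that ITT sees is

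p_obs = p(1 − L) / [(1 − L) + rL],

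and

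P(declare non-inferiority) = Φ( (p_obs,cyt − p_obs,NRT + 0.05) / SE − 1.96 ),

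SE = √{ [p_obs,NRT(1 − p_obs,NRT) + p_obs,cyt(1 − p_obs,cyt)] / 655 }.

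Worked example, 20% loss in both arms and r = 1: the observed rates are 0.40 and 0.36, the difference is −0.04 and SE = 0.0268. Then 0.01/0.0268 − 1.96 = −1.587, giving 5.6%.

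| Loss NRT / cytisine | r = 1 | r = 0.5 | r = 0.25 | r = 0 (all lost smoke) |
|---|---|---|---|---|
| 10% / 10% | 3.8% | 3.1% | 2.8% | 2.5% |
| 20% / 20% | 5.6% | 4.0% | 3.2% | 2.5% |
| 30% / 30% | 8.3% | 5.1% | 3.7% | 2.5% |
| 20% / 15% | 22.5% | 10.3% | 5.7% | 2.5% |
| 20% / 10% | 52.8% | 21.3% | 9.1% | 2.5% |
| 10% / 20% | 0.03% | 0.24% | 0.75% | 2.5% |

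**3. Requiring both sets.** Simulation with 400,000 replicates; per protocol is taken as those not lost, and loss is unrelated to quit status (r = 1).

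| True rates | Loss NRT / cytisine | ITT alone | Per protocol alone | Both |
|---|---|---|---|---|
| 50% v 45% | 20% / 20% | 5.7% | 2.5% | 2.2% |
| 50% v 45% | 20% / 10% | 52.8% | 2.5% | 2.5% |
| 50% v 55% | 10% / 10% | 93.3% | 93.1% | 91.5% |
| 50% v 55% | 20% / 20% | 90.8% | 90.0% | 87.4% |

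The first two rows show false claims, the last two power. The simulation does not model bias from selecting participants on compliance.

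**4. Order of events.** The review has an end point (the primary analyses) but no link to unblinding. The code may be broken once the last follow-up call is recorded, which also comes before the primary analyses. Nothing puts the review first. Data analysis says that the existing plan specifies all analyses in advance, yet the review may change that plan.

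**The case against.** The strongest reply is that a statistical analysis plan exists and is not shown. A rule for discordant results, compliance thresholds, sign-off dates and missing-data sensitivity analyses are what a condensed article leaves to it. That is fair, and their mere absence is not the point. What stands is wording that the article does fix: the primary test and its missing-data rule, a per-protocol result that is only weighed, and a later review that may amend the unseen plan. The unseen plan cannot settle the timing, because the review comes after it.

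Three stronger readings are tempting, and the article does not support them.

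- A reader might infer that the per-protocol result plays no part in the decision. It has a part, and its population is outlined; what is undefined is how much it counts and how the outline is applied.
- A reader might infer that the review will be unblinded. The article permits that order but does not plan it. The stated reason for reopening the plan is recent research, not trial data, and the covariate adjustment it mentions belongs to secondary analyses.
- A reader might infer that the error rate is simply uncontrolled. It depends on how much loss occurs, in which arm, and on how many of the lost are abstinent. Nothing in the article suggests that NRT will lose more people. With heavier cytisine loss the test is conservative.

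It is also fair that choosing a one-month outcome already limits loss, and that the joint rule is no guarantee, since a set selected on compliance can be biased itself.

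**Conclusion.** The point holds as a weakness in the decision rule and in the timing of the review. At a true 5-point deficit the ITT test keeps its 2.5% error if every lost participant smokes. At 20% equal loss the inflation is modest, 3.2% to 5.6%. It becomes serious (9% to 53%) if NRT loses 20% and cytisine 10%. Under the reverse imbalance the error falls to between 0.03% and 0.75%. The ranges cover r from 0.25 to 1, and all loss rates are assumptions. Participants know their treatment, so unequal loss in either direction is plausible. This should be changed: the remedy is cheap and the sample for it is already in the design. It does not show that the trial's conclusion will be wrong.

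**What to change.** 1. State that non-inferiority is claimed only if the lower 95% limit for cytisine minus NRT lies above −5 points in both the ITT and the per-protocol sets.
2. Require the per-protocol rules and any amendment to the analysis plan to be signed and dated before the code is broken, by staff without access to allocation.
3. Add an ITT sensitivity analysis that varies the missing-equals-smoking rule separately by arm and reports the tipping point. This is needed alongside item 1 because of the possible selection bias in the per-protocol set.

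Cost: wording, one extra analysis, and a claim that is somewhat harder to win. At the design rates (50% v 55%) the joint rule has about 91.5% power at 10% loss and 87% at 20%, about 3 points below the 90% target in the latter case. Sample size and trial conduct do not change.
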